**What impact does the New Zealand maternity care model have on fetal and neonatal outcomes? A retrospective cohort study comparing exclusive midwife led care with a shared care model.**

Background

New Zealand has a maternity system that has undergone a number of changes in the past twenty years that have moved it away from a medical model of care and towards a midwifery model [18]. The changes have been the subject of scrutiny and controversy focusing on questions related to the safety of the system [3, 5, 6, 7, 15, 16, 17, 20, 22]. Despite this, there has been little in the way of systematic evaluation that specifically relates to the safety of the maternity system [8, 10-14, 19].

New Zealand’s maternity system is based on a midwife-led care model, whereby midwives practice with a level of autonomy higher than most of their overseas counterparts [9, 21, 23]. International literature has generally supported the safety of the midwife-led care model [4]. However this does not provide sufficient evidence to support the safety of the New Zealand system, as in many countries where the international literature was based midwives have less autonomy than they do in New Zealand; so even in midwife-led births there is some medical input. The uniqueness of our system means that evaluation of the safety of New Zealand based midwife-led care needs to be addressed within New Zealand.

Along with the lack of New Zealand based research, impetus for research in this area has been provided by a recently published Dutch study [1]. Holland has a maternity system that is similar to ours in that midwives practice with a high level of autonomy; therefore evaluation in a Dutch context is relevant to us. The Dutch study found, most significantly, that “*infants of pregnant women at low risk whose labour started in primary care under the supervision of a midwife had a significant higher risk of delivery related perinatal death than infants of pregnant women at high risk whose labour started in secondary care under the supervision of an obstetrician… relative risk 2.33*” [1, p. 1]. Given the similarities between the Dutch maternity system and ours, this is a concerning finding in the New Zealand as well as Dutch context.

In contrast, further incentive for addressing the lack of New Zealand based research is provided with the demonstrated value of midwifery led care. Consumer satisfaction surveys have reported high levels of support for our current model [6]. The most recent (2011) survey reported on 3225 women; 89% of these women reported feeling satisfied or very satisfied with the care they received from their LMC. This is encouraging in terms of midwife-led care as three quarters of respondents were registered with a self-employed midwife as their LMC [6].

However, the media, consumer and professional opposition may have led to a decrease in women’s confidence of the system and has been reported as being discouraging to midwives [2]. Midwives have not had an evidence base to defend the current model, which has exacerbated the critique. If evidence can be produced that provides support for the safety of the current maternity system, then this can be used by midwives to defend their profession, and to generate support, and increase consumer confidence.

If however the study finds similar results to the Dutch study, in that midwife-led care leads to poorer outcomes for babies compared with medical care, this evidence can be used as incentive to generate further research that focuses on the reasons for this, with the aim to alleviate the causes and improve outcomes for babies.

Ultimately a safer maternity system that supports the best possible outcomes for babies is an important goal. Midwifery care is an essential part of our maternity system and it is essential for its continuation that it be based on evidence with its safety ensured.

Aim

This study aims to evaluate key aspects of the safety of the New Zealand maternity system. Specifically we will investigate serious fetal and neonatal outcomes that are potentially related to care provider.

Objectives

i) To review the literature regarding the safety of midwife-led care models within New Zealand and internationally.

ii) To demonstrate what data is available for the purpose of reviewing safety related fetal and neonatal outcomes in relation to maternity care provider, within New Zealand.

iii) To calculate and compare (where relevant) the incidence of potentially avoidable serious early neonatal morbidity and perinatal mortality, overall, and 1) in women whose LMC is reported as being a midwife where there is no evidence of medical input, 2) in women whose LMC is reported as being a midwife where there is evidence of medical input and 3) in women whose LMC is a general practitioner or obstetrician.

Inclusion criteria

- Singleton pregnancy
- Delivered during a specified time period (likely to be 1^st^ January 2006 and 1^st^ January 2010, The final inclusion period will be based on DHB birthing numbers and required sample size)
- Birthed at one of six specified District Health Boards
- Equal to or greater than 37 weeks gestation
- No identified major fetal or neonatal congenital, chromosomal, or metabolic abnormalities.

The sample size has been determined based on power calculations using the rarest outcome in the study, intrapartum fetal death. Sample size has been calculated using the Fleiss method with continuity correction in OpenEpi. Outcome rates have been estimated based on the Dutch Perinatal Mortality Study. An adequately powered simple study requires a sample size of 48 878. However, we need to increase the sample size because we wish to adjust the results for several major confounders particularly maternal age, antenatal risk, ethnicity, deprivation and parity of the mother. Furthermore, we wish to perform some subgroup analysis. For these reasons, we plan to double the sample size.

Exposure

- Reference group

Women who are reported to have a midwife as Lead Maternity Carer at booking and at admission in labour and where there is no evidence of medical input.

- Comparison groups

Women who are reported to have a midwife as LMC with evidence of medical input. Women will be included in this group if they have had one or more secondary care consultations or if they have had any antenatal admissions to hospital.

- Women who have had a General Practitioner, private obstetrician, or secondary care team as their LMC.

Outcomes

- Antepartum stillbirth: Antepartum stillbirth rates will be calculated as the number of fetal deaths that occur before the onset of labour divided by the total number of births in our cohort.
- Intrapartum mortality: Intrapartum mortality rates will be calculated as the number of fetal deaths that occur after the onset of labour but before delivery divided by the total number of births in our cohort, not including antenatal still births.
- Early neonatal mortality: Early neonatal mortality rates will be calculated as the number of early neonatal deaths, that is deaths that occur post-delivery and within seven days of life, divided by total number of births in our cohort, not including antenatal still births or babies who have died in the intrapartum period.
- Neonatal admission to a specialist neonatal unit: Neonatal admission rates will be calculated as the number of babies admitted to a specialist neonatal unit within the first seven days of life divided by the total number of births in our cohort but not including antenatal stillbirths, or babies dying intrapartum, or in the early neonatal period.
- Low Apgar score: Rates of low Apgar score will be calculated as the number of babies born with an Apgar score at five minutes post-delivery of below seven, divided by total number of births in our cohort, not including antenatal still births or babies who have died in the intrapartum period.
- Birth related asphyxia: Rates of birth related asphyxia will be calculated based on the number of babies identified with the condition by ICD-10-AM codes P210, P211, P219, divided by total number of births in our cohort, not including antenatal still births or babies who have died in the intrapartum period.
- Intrauterine hypoxia: Rates of intrauterine hypoxia will be calculated based on the number of babies identified with the condition by ICD-10-AM codes P200, P201, P209 divided by total number of births in our cohort, not including antenatal still births or babies who have died in the intrapartum period.
- Hypoxic ischaemic encephalopathy: Rates of hypoxic ischaemic encephalopathy will be calculated based on the number of babies identified with the condition by ICD-10-AM code P916, divided by total number of births in our cohort, not including antenatal still births or babies who have died in the intrapartum period.
- Low birth weight: Where the birth weight was recorded as less than 2500 grams. This variable was included as a negative control outcome in order to determine whether adjustment for confounding for the main outcomes was likely to have been sufficient. This is on the assumption that model of care is unlikely to substantially affect birth weight directly, but similar confounders may affect the relation between low birth weight, model of care and the outcomes

Covariates

The study will collect a number of maternal variables that may be potential confounders or mediators. These include:

- Maternal age: 12-18 yrs; 19-25 yrs; 26-35 yrs; 36-40 yrs and 40+.
- Ethnicity: NZ European, Māori, Pacific Island, Asian, Other.
- Deprivation: NZ Dep quartiles.
- Parity before delivery: 0, 1, 2, 3, 4+.
- Gestation at delivery: 37/40-38/40; 39/40-40/40; 41/40; 42+ weeks.
- Location of delivery: Primary birthing unit, secondary or tertiary hospital.
- Mode of delivery: Normal vaginal delivery, instrumental delivery, caesarean section.
- Pre-existing diabetes and/or hypertension: yes, no.

Analysis

- We will first calculate incidence rates (and 95% confidence intervals) of all outcomes for all groups combined and then for each group separately.
- We will then develop logistic regression models to calculate odds ratios (and 95% confidence intervals) for each major outcome comparing women receiving shared compared with midwife only care. The models will include potentially confounding patient characteristics such as age, parity, ethnicity and presence of pre-existing conditions.

Available data

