1. OUTCOMES

Outcomes are also collected from the MOH’s NMDS. We may need to use the Perinatal Maternal Mortality Review Committee Data to ascertain antepartum vs. intrapartum stillbirth as MOH data may not be sufficiently detailed.

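### Objective iii names perinatal mortality, but the Outcomes section defines only three separate death outcomes and no combined estimate

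*SAP*

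**What the plan says.** Four parts of the SAP bear on this.

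- **Background.** The Dutch study is given as impetus for the research. Its quoted finding is that infants in midwife-supervised primary care "had a significant higher risk of delivery related perinatal death", with a relative risk of 2.33. That is the only effect size in the SAP. The Background later says how a matching finding would be used: "If however the study finds similar results to the Dutch study", which the same sentence explains as midwife-led care leading to poorer outcomes for babies.
- **Objective iii and Appendix 1.** The objective is to calculate and compare the incidence of "potentially avoidable serious early neonatal morbidity and perinatal mortality", overall and by care group. The outcome node of the graph in Appendix 1 is perinatal mortality and morbidity.
- **Outcomes and Analysis.** Deaths appear as three rates: antepartum stillbirth, intrapartum mortality and early neonatal mortality, each with its own denominator. Incidence is planned for all outcomes, and a logistic model for each major outcome. No combined death outcome is defined.
- **Sample size paragraph and Available data.** The SAP states: "The sample size has been determined based on power calculations using the rarest outcome in the study, intrapartum fetal death". On separating antepartum from intrapartum stillbirth, the outcomes part of Available data says that "MOH data may not be sufficiently detailed" and that mortality review committee data may be needed.

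**The concern.** The plan names a mortality outcome in its objective and its causal graph and then does not define it. Followed as written, the analysis gives up to three adjusted odds ratios for death, each from very few events, and none for perinatal death as a whole.

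Three things are at stake.

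- **Precision.** Rare deaths are divided among three models, although some of the information could be pooled at no cost in data.
- **Robustness.** A stillbirth assigned to the wrong side of labour onset moves between antepartum stillbirth and intrapartum mortality and distorts both. No planned mortality outcome combines the two.
- **Pre-specification.** The safety question is contested. If the separate results are sparse and deaths are then combined, the combination will look chosen after the fact.

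**Working it through.** **1. Outcomes side by side**

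| Death outcome | Denominator in the SAP | Depends on antepartum/intrapartum timing? |
|---|---|---|
| Antepartum stillbirth | all births | yes |
| Intrapartum mortality | births less antepartum stillbirths | yes |
| Early neonatal mortality | births less both of the above | no (both kinds of fetal death are excluded) |
| Perinatal mortality (objective iii) | not defined | would not |
| Delivery-related perinatal death (Background) | not defined | would |

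With deaths this rare the denominators are almost equal, so a crude combined rate could be approximated from the three counts. A combined adjusted odds ratio and its confidence interval cannot be obtained from three separate models.

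**2. Can the sample size be reproduced?**

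The SAP gives the method ("Sample size has been calculated using the Fleiss method with continuity correction in OpenEpi"), the source of the rates ("Outcome rates have been estimated based on the Dutch Perinatal Mortality Study") and the result ("An adequately powered simple study requires a sample size of 48 878"). It does not give the two rates, the effect, alpha, power or allocation ratio, nor whether the figure is a total. I assume a total, two equal groups, two-sided alpha 0.05 and 80% power. With d = p1 − p0 and p̄ the mean of p0 and p1, the size per group is

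m = [1.960·√(2p̄(1−p̄)) + 0.842·√(p0(1−p0) + p1(1−p1))]² / d²

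n = (m/4)·[1 + √(1 + 4/(m·d))]²

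Taking RR 2.33 and solving backwards gives p0 = 0.000664 and p1 = 2.33 × 0.000664 = 0.001547. Then m ≈ 22 227, n ≈ 24 439 and the total is 48 878.

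This is not a confirmation, because other pairs of rates return the same total to within rounding:

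| RR | Rates per 1000 |
|---|---|
| 2.0 | 1.04 v 2.08 |
| 2.33 | 0.66 v 1.55 |
| 3.0 | 0.36 v 1.08 |

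At 90% power, RR 2.33 fits with 0.87 v 2.02 per 1000. The figure therefore does not show which outcome or effect was used.

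**3. What a combined outcome would gain**

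The anchor is an assumption: an intrapartum rate of 0.664 per 1000 in the lower-risk group, RR 2.33, and the settings above. The planned size is 2 × 48 878 = 97 756. Let k be the frequency of the combined outcome relative to intrapartum death.

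| k | Total needed at RR 2.33 | RR detectable at 97 756, 80% power |
|---|---|---|
| 1 (intrapartum alone) | 48 878 | 1.86 |
| 1.5 | about 32 600 | 1.68 |
| 2 | about 24 400 | 1.57 |
| 3 | about 16 300 | 1.45 |

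**4. When the gain is lost**

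If the combined RR is weaker, the need rises. At k = 2 it is about 38 300 for RR 2.0, 61 600 for RR 1.75 and 124 000 for RR 1.5, the last exceeding the plan.

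Suppose the whole effect lies in intrapartum death and the other deaths have RR 1. The combined RR is then (2.33 + k − 1)/k:

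- k = 2: 3.33/2 = 1.67, still above the detectable 1.57.
- k = 3: 4.33/3 = 1.44, just below the detectable 1.45.

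Dilution is therefore possible, and the components must stay visible.

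**The case against.** The strongest defence is that nothing essential is missing. Intrapartum and early neonatal mortality are both listed with explicit denominators, and reporting causes of death separately is defensible. The Dutch study is motivation and a source of rates. No replication is planned, and the SAP's reference to similar results is directional. The Dutch contrast, low-risk primary care against high-risk secondary care at the onset of labour, also differs from this study's exposure groups, so a matching endpoint would not make a direct replication. The timing problem is anticipated and a second data source is named.

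Most of this stands, and it limits the point. It does not explain why an outcome named in objective iii has no definition or planned estimate. Naming a possible second source does not make the results independent of timing.

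A reader might infer two stronger things.

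- **That the study was mis-sized**, with the Dutch combined-outcome effect or rates attached to intrapartum death, so that real power is far lower. The documents do not support this. A match to 48 878 at RR 2.33 is circular, since the baseline rate was solved to produce it. Any power loss would also need an assumed intrapartum share of combined deaths, which the SAP does not give. Sizing on the rarest outcome is not an error, and at equal RR it over-provides for a more frequent one.
- **That the plan cannot address the Dutch finding at all.** This too is excessive. The likely components are analysed; only the combined estimate is absent.

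**Conclusion.** The point holds as a gap between objective and outcomes. Perinatal mortality is promised, and three separate rare outcomes are delivered, two of them resting on a timing distinction that the SAP itself doubts. Under the assumed anchor and equal RR, a combined outcome 1.5 to 3 times as frequent lowers the detectable RR at 97 756 from 1.86 to between 1.68 and 1.45. These figures are unadjusted and assume equal groups. They show the direction and rough size of the gain and do not predict this study's power. The gain shrinks or disappears if the effect is confined to one type of death.

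No fault is found with sizing on intrapartum fetal death, and 48 878 stays unverified in either direction. The point is a cheap improvement.

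**What to change.** Add two derived outcomes to the Outcomes section, and to both the incidence and the logistic analyses:

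- **(a) Intrapartum plus early neonatal death**, with births excluding antepartum stillbirths as denominator. I assume this is closest to the Dutch outcome. The SAP does not define that term, so the sponsor should confirm it.
- **(b) Total perinatal death** (antepartum, intrapartum and early neonatal), with all births as denominator. This does not depend on antepartum versus intrapartum timing and serves as a check on (a), which does.

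Keep the three components and report them beside the combined outcomes.

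The cost is a few lines of text and two variables derived from deaths already being collected. The small downside is that a composite mixes types of death and may dilute an effect confined to one of them, which is why the components remain.

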1. COVARIATES

All covariate data will be collected from the MOH. The covariates listed above are routinely collected, after hospital discharge, as part of the National Minimum Dataset (NMDS).

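### Antenatal risk is named as a major confounder to adjust for, but it is never defined and the listed covariates represent it only crudely

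*SAP*

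**What the plan says.** The sample size paragraph (SAP, Inclusion criteria) states that "An adequately powered simple study requires a sample size of 48 878" and that this must grow because the authors wish to "adjust the results for several major confounders particularly maternal age, antenatal risk, ethnicity, deprivation and parity of the mother". It then adds a second reason: "Furthermore, we wish to perform some subgroup analysis. For these reasons, we plan to double the sample size".

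Under Covariates, the only medical-risk entry is "Pre-existing diabetes and/or hypertension: yes, no". The list is introduced as non-exhaustive and as a mixture of possible confounders and mediators. The model sentence under Analysis gives examples of what will be included: age, ethnicity, parity and pre-existing conditions. It mentions neither antenatal risk nor deprivation.

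On sources, the SAP says "All covariate data will be collected from the MOH" and describes the listed items as routinely held in the national discharge dataset. The diagram in Appendix 1 shows pre-existing conditions without restriction, and also BMI, smoking and trimester of registration. Those last three are not in the covariate list.

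Under Exposure, a woman with a midwife as lead carer moves from the reference group to the shared-care group if she has had any consultation in secondary care or any antenatal hospital admission.

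**The concern.** Women are referred or admitted largely because of risk, so the exposure is itself a marker of risk. Higher-risk histories will gather in the shared-care group by construction. Confounding by antenatal risk is therefore the main threat to the shared v midwife-only odds ratio, and it is the one named confounder without a variable of its own.

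The direction matters. Unadjusted risk raises adverse outcomes in shared care and so flatters midwife-only care. That could mask the kind of signal that prompted the study: the Background cites a Dutch cohort with "relative risk 2.33" for low-risk women starting labour under a midwife against high-risk women starting under an obstetrician. The Background also says that supportive findings would be used to defend the present system. A result described as adjusted for antenatal risk would carry more weight than the listed covariates can justify.

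**Working it through.** **1. The plan's own figure.** The method is given ("Sample size has been calculated using the Fleiss method with continuity correction in OpenEpi") and the rates are attributed ("Outcome rates have been estimated based on the Dutch Perinatal Mortality Study"), but the rates themselves, alpha, power and group ratio are not printed. The figure of 48 878 can therefore be neither confirmed nor refuted. If one assumes a risk ratio of 2.33 (printed for delivery-related perinatal death, not intrapartum death alone), two-sided alpha 0.05, equal groups and the continuity correction, 48 878 corresponds to rates of about 0.66 v 1.55 per 1000 at 80% power, or 0.87 v 2.02 per 1000 at 90%. Doubling gives 2 × 48 878 = 97 756. Nothing here turns on that number, because a larger sample narrows the interval around a confounded estimate without moving it.

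**2. The named confounders, side by side.**

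| Named in sample size paragraph | Entry under Covariates | Named in model sentence |
|---|---|---|
| Maternal age | Yes | Yes |
| Ethnicity | Yes | Yes |
| Parity | Yes | Yes |
| Deprivation | Yes | No |
| Antenatal risk | None; nearest is the diabetes/hypertension flag | No; nearest is pre-existing conditions |

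The remaining listed covariates (gestation at delivery, place and mode of delivery) are settled at or near birth and cannot stand for risk at booking. Consultations and antenatal admissions are used up in defining exposure.

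**3. Possible size of the bias.** For a binary risk factor left out of the model, with prevalence p1 in shared care, p0 in midwife-only care and risk ratio RR for the outcome:

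bias factor = [1 + p1(RR − 1)] / [1 + p0(RR − 1)]

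All inputs are assumed; the SAP gives none.

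- Central: p1 = 0.35, p0 = 0.10, RR = 2: 1.35 / 1.10 = 1.23
- Low: p1 = 0.20, p0 = 0.05, RR = 1.5: 1.10 / 1.025 = 1.07
- High: p1 = 0.45, p0 = 0.10, RR = 3: 1.90 / 1.20 = 1.58

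In the central case a true shared v midwife-only ratio of 1/1.23 = 0.81 would appear as 1.00.

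**4. How much the existing flag helps.** Use a second assumed set: high risk in 50% of shared care and 20% of midwife-only care, RR = 2. With no adjustment the factor is 1.50 / 1.20 = 1.25. Suppose the flag identifies a share s of high-risk women and never flags a low-risk woman. Among unflagged women the prevalence becomes p(1 − s)/(1 − ps).

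- s = 0.10: 0.474 v 0.184, factor 1.474 / 1.184 = 1.25 (1.245 before rounding)
- s = 0.25: 0.429 v 0.158, factor 1.429 / 1.158 = 1.23
- s = 0.50: 0.333 v 0.111, factor 1.333 / 1.111 = 1.20

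With RR = 3 the unadjusted factor is 2.00 / 1.40 = 1.43, and the three values are 1.42, 1.41 and 1.36. Under these assumptions, even a flag that catches half of the high-risk women leaves most of the bias in place.

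**The case against.** The strongest reply is that the plan is more open than a literal reading suggests. The covariate list and model sentence are both illustrative, the diagram shows unrestricted pre-existing conditions together with BMI, smoking and trimester of registration, and age and parity carry part of antenatal risk. A reader might infer that the diabetes/hypertension flag is the only baseline risk information and that adjustment is impossible. The documents do not support that: further variables are not excluded, and partial adjustment is available. What stands is that an open list neither defines nor sources the variable. The SAP states a source only for the covariates it lists, and the diagram and list disagree.

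Second, low birth weight is planned as a negative control outcome to judge whether adjustment was sufficient. This is a real safeguard. It may detect confounding that also acts on birth weight, but it does not correct it, and risks unrelated to birth weight could pass unseen.

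Third, one might infer that the doubling depends on antenatal risk. It does not: four other confounders and subgroup analysis are also given as reasons.

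Fourth, one might suspect that the flag is recorded more completely in shared care, where women may have more hospital discharges. The SAP does not say which discharges supply the flag, so this is conjecture and forms no part of the finding.

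Finally, the bias inputs are all assumed, and the formula in step 3 gives no credit to age, parity or the flag. It shows what could happen, not what this cohort will show.

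**Conclusion.** The point holds as a defect of specification with a material consequence. The SAP promises adjustment for antenatal risk, does not define it, omits it from the model sentence, and lists only a coarse flag that represents it directly. Because exposure is defined by secondary care contact, following the listed covariates would leave residual confounding in the main odds ratio, tending to favour midwife-only care. An illustrative bias factor is 1.23, with a range of 1.07 to 1.58. These values rest on assumed prevalences and risk ratios, on a single binary risk factor treated as wholly unmeasured, and on outcomes rare enough for an odds ratio to approximate a risk ratio. The conclusion is that adjustment is undefined and crude, not that it cannot be made. No change to the sample size follows.

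**What to change.** - Add to the covariate list and the main model a booking-time antenatal-risk variable built from history that predates exposure: for example previous caesarean, previous stillbirth or neonatal death, and major chronic disease including diabetes and hypertension.
- State its codes and source. Ascertain it by the same rule for every woman, and not from the antenatal admissions that define exposure.
- Align the covariate list, the model sentence and Appendix 1. Give BMI, smoking and trimester of registration a source and an entry, or explain their absence. Name deprivation in the model sentence.
- If Ministry of Health data cannot supply obstetric history, withdraw the statement that results are adjusted for antenatal risk, report this as a limitation, and add a quantitative bias analysis with stated inputs.

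The cost is a longer code list in the data request and one further model term, provided the data exist. Availability must be confirmed first, because the SAP vouches only for the covariates it lists. Discharge coding of obstetric history may be incomplete, so some residual confounding would remain and the negative control should be kept.

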1. EXPOSURE

For classifying the exposure status LMC data will be collected from individual DHBs. This category is the only one not available from the MOH who only hold LMC data for around 70% of women.

It is difficult to know how robust/complete the DHB data is before accessing it. Generally it is entered by clinicians. The available categories are as follows:

- LMC data:

LMC at booking

LMC at admission in labour

Labour care provided by*

Delivered by

Labour and delivery assisted by

*The last three are not collected by all the DHBs.

- Data to classify ‘medical input’:

A woman will be classified as having medical input if she has had antenatal secondary care consultations. This data is held by the MOH and comes from the National Non- Admitted Patient Collection. We will analyse the number of secondary care consultations and the type of consultation. The following codes are relevant:

| W03002 | First obstetric consults |
| --- | --- |
| W03003 | Subsequent obstetric consults |
| W03005 | Amniocentesis |
| W03006 | Chorion villis sampling |
| W03007 | Rhesus Clinics - multidisciplinary clinics |
| W03008 | Maternity foetal medicine clinics - multidisciplinary clinics |
| W03009 | Foetal medicine / anomalies clinics - multidisciplinary clinics |

Some of these categories are more likely to be associated with greater obstetric input; number of consults is also relevant. For example a woman who has one consult recorded under amniocentesis and no further consults likely had a negative test and limited obstetric input in her care. Sub-category analysis will therefore be necessary.

The number of obstetric related hospital admissions within the pregnancy is also available from the NMDs. These data are not detailed and we will be making the assumption that if a patient has been admitted to hospital she will have had some level of secondary care input. Again number of admissions is relevant and sub-category analysis necessary.

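### Exposure is set by consultations, admissions and labour carer recorded after booking, so the shared versus midwife-only odds ratios are expected to be confounded by indication, by an amount the SAP does not let us determine

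*SAP*

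**What the plan says.** Under Exposure, the reference group is "Women who are reported to have a midwife as Lead Maternity Carer at booking and at admission in labour", with the further condition of no medical input. A woman with a midwife LMC goes to the first comparison group "if they have had one or more secondary care consultations or if they have had any antenatal admissions to hospital". The second comparison group has a general practitioner, private obstetrician or secondary care team as LMC.

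Available data, 1. EXPOSURE repeats the rule: "A woman will be classified as having medical input if she has had antenatal secondary care consultations". On admissions it says: "These data are not detailed and we will be making the assumption that if a patient has been admitted to hospital", some secondary care input will have followed. Neither section sets a gestational cut-off, separates reasons for referral, or requires the event to precede the outcome. Sub-category analysis by number and type of consultation, and by number of admissions, is promised.

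Under Analysis, logistic models give odds ratios "for each major outcome comparing women receiving shared compared with midwife only care". On adjustment: "The models will include potentially confounding patient characteristics such as age, parity, ethnicity and presence of pre-existing conditions". The one medical-risk item under Covariates is "Pre-existing diabetes and/or hypertension: yes, no". The sample-size paragraph under Inclusion criteria also names antenatal risk as a major confounder to be adjusted for, but it is not defined there and does not appear under Covariates. Low birth weight is a negative control outcome. The diagram in Appendix 1 has no node for complications arising during pregnancy.

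**The concern.** A woman is in the reference group only if nothing in her pregnancy led to a recorded consultation or admission, and if her LMC was a midwife both when she booked and when labour began. In a midwife-led system, a consultation or admission is a natural response to an emerging problem. Membership of the shared group is then partly a marker of risk that arose after care began, and that same risk raises the probability of the outcomes. This is confounding by indication built into the exposure definition, so doubling the sample does not reduce it.

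The expected direction matters. The Background motivates the study by a Dutch relative risk of 2.33 against midwife-led care. The bias here runs the other way, so a real harm could be diluted or hidden. The Background also says that supportive results would be used to defend the current system.

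For antepartum stillbirth there is a sharper problem. Nothing stops a consultation or admission prompted by the fetal death from placing the woman in shared care.

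**Working it through.** **What can be checked against the SAP's own figures.** The SAP gives no complication prevalence, referral rate or risk ratio, so it has no bias figure to reproduce. Its sample size of 48 878 cannot be rebuilt either, because the outcome rates, alpha, power and group ratio are not stated. The point does not depend on it.

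**Model, with no true effect of care.** All inputs are assumptions:

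- q: proportion of pregnancies that develop a complication the covariates do not capture
- r: risk ratio for the outcome given that complication
- s1, s0: probability of a consultation or admission with and without it
- p0: outcome risk without it, 1 per 1000

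**Formulas**

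- Proportion in shared care: f = q·s1 + (1 − q)·s0
- Complicated share, shared group: qS = q·s1 / f
- Complicated share, midwife-only group: qM = q·(1 − s1) / (1 − f)
- Risks: pS = p0·[1 + qS·(r − 1)] and pM = p0·[1 + qM·(r − 1)]
- OR = [pS/(1 − pS)] / [pM/(1 − pM)]

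**Middle case in full** (q 0.2, r 2, s1 0.9, s0 0.3)

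- f = 0.18 + 0.24 = 0.42
- qS = 0.18/0.42 = 0.429
- qM = 0.02/0.58 = 0.034
- Risks 1.429 and 1.034 per 1000, OR 1.38

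| q | r | s1 / s0 | qS | qM | Shared, per 1000 | Midwife-only, per 1000 | OR |
|---|---|---|---|---|---|---|---|
| 0.10 | 1.5 | 0.7 / 0.3 | 0.206 | 0.045 | 1.10 | 1.02 | 1.08 |
| 0.20 | 2 | 0.9 / 0.3 | 0.429 | 0.034 | 1.43 | 1.03 | 1.38 |
| 0.25 | 3 | 0.8 / 0.2 | 0.571 | 0.077 | 2.14 | 1.15 | 1.86 |
| 0.30 | 3 | 0.9 / 0.2 | 0.659 | 0.051 | 2.32 | 1.10 | 2.11 |
| 0.35 | 4 | 0.9 / 0.2 | 0.708 | 0.063 | 3.12 | 1.19 | 2.63 |

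A milder grid (q 0.1 to 0.3, r 1.5 to 3, s1/s0 of 0.7/0.3, 0.9/0.3 or 0.9/0.2) gives 1.08 to 2.11. A stronger one (q 0.15 to 0.35, r 2 to 4, s1 0.7 to 0.9, s0 0.20 to 0.25) gives 1.25 to 2.63. If grouping does not depend on the complication (s1 = s0), or the complication is fully adjusted for, the OR is 1.00.

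**Chance of a spurious significant excess in shared care.** This uses 2 × 48 878 = 97 756 women, all taken to fall in these two groups, a two-sided 5% test and a normal approximation. At 1 per 1000 the chance is 6% in the first row, 42% in the second and 99% in the fourth. For an outcome with an assumed 3% baseline risk it is 53% in the first row and about 100% in the second. Women in the third exposure group would lower these figures.

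**Masking.** If midwife-only care truly had an odds ratio of 2.33 against shared care, the middle case would show about 2.33/1.38 = 1.69. The 2.33 is borrowed for scale only: it was a relative risk from a different comparison.

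**The case against.** The SAP is alert to confounding. It names antenatal risk as a major confounder, and its covariate list is open-ended, so adjustment could be added. It includes a negative control outcome to test whether adjustment was sufficient. It recognises that a single consultation may mean little obstetric input. Restriction to singleton term pregnancies without major abnormality removes some high-risk women. The title asks about exclusive midwife-led versus shared care, and a contrast by booked LMC answers a different question.

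Much of this stands as context, but it does not repair the definition. An undefined and unlisted confounder cannot be adjusted for as planned. Low birth weight can only flag a problem, may miss indications unrelated to birth weight, and has no stated consequence if it signals one. Sub-category analysis grades the amount of input and not the reason for it.

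A reader might infer three stronger things that the SAP does not support:

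- That the odds ratios are certain to favour midwife-only care, or that the study cannot address its title question. The direction is expected, but the size is unknown and could be small, as the first row of the table shows.
- That adjusting for complications is wrong because they arise after care begins. Under the SAP's own exposure, a complication that prompts the first consultation or admission comes before exposure and acts as a confounder. Only later ones raise that difficulty.
- That no adjustment for antenatal risk is intended. It is intended, but not specified.

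**Conclusion.** The concern holds in this form. Exposure depends on events after booking that are likely to reflect emerging complications, and nothing specified in the plan captures those complications. Each shared versus midwife-only odds ratio (the SAP plans one per major outcome, not a single main one) is expected to be biased towards making midwife-only care look safer. For antepartum stillbirth, exposure can also be set by the outcome.

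The mechanism follows from the SAP's text. The size does not: about 1.08 to 2.63 under no true effect, 1.38 in a middle case, and every input is assumed. I read shared care in the Analysis section as midwife LMC with medical input. The labour-carer element rests on the reference-group rule alone ("at booking and at admission in labour and where there is no evidence of medical input").

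This needs correcting before analysis, because the fault is in the exposure definition and a less biased grouping can be built from a field already planned.

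**What to change.** 1. Add an analysis by LMC at booking: midwife versus general practitioner, private obstetrician or secondary care team, stating explicitly where the secondary care team group is placed. Analyse women as booked, whatever consultations, admissions or transfers follow. Adjust for characteristics present at booking, and base causal statements about the model of care on this analysis.
2. Keep the contrast in the title. Either report it as descriptive and not causal, or adjust it for named complications dated before the first consultation or admission.
3. Define antenatal risk, list it under Covariates, and add complications arising in pregnancy to the Appendix 1 diagram.
4. Do not count consultations or admissions at or after diagnosis of fetal death when assigning exposure.

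**Cost.** LMC at booking is already a planned District Health Board field and is not among the three that some boards do not collect. The first item therefore needs SAP wording and a recoded variable, but the SAP says completeness of these data is unknown, so it must be confirmed. The second option under item 2 needs dated diagnoses, and the SAP warns that the admission data lack detail. The causal contrast becomes the booked model and not exclusive midwife care. Group sizes change, so precision must be rechecked. Selection at booking remains and can be reduced only through characteristics measured at that point.
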